**Fig. 3 Fig3:**
[figure not shown]
Schedule of enrolment, interventions, and assessments

#### Plans to promote participant retention and complete follow-up

Participants are sent the questionnaires either by post or via an online survey, according to participant preference. When posting the questionnaire, researchers will also send the participant a self-addressed envelope, a pen, and an unconditional gift voucher of £5 at all time-points. The consent form will only be posted at baseline. Participants who complete the questionnaire online will be sent a link to complete the questionnaire via email. Non-responders at each time point will be telephoned to check whether they have received the questionnaire, and automated reminders are sent for online questionnaires. If it is established that the participant is unable or unwilling to fully complete the questionnaires, the study team will offer the participant the option of completing only the FACT-G, the EQ-5D-5L, and the CSRI, as they are needed to evaluate the primary outcomes (effectiveness and health economic) and cost per QALY. A primary outcome CRF has been developed for this purpose. Researchers will also offer participants the opportunity to complete these outcomes over the telephone when appropriate.

#### Data management

The SURECAN study team will work closely with staff at participating sites to ensure accurate (complete, valid, and reliable) collection of data. Completeness, range, and consistency checks will further enhance the quality of the data. Two levels of data validation will be incorporated when entering data (either online via direct participant data entry or entered directly onto the REDCap database by the study team). The first level will aim to prevent obviously invalid data from being entered, e.g. entering a date of birth that occurred after the date of consent. The second level checks for data completeness include any unusual data entered, i.e. a variable that was outside of the pre-defined range. The site PI is responsible for ensuring that all data queries are resolved. Ongoing data entry, validation at adherence to the trial protocol at sites will be closely monitored by the study team, and any concerns will be raised to the participating sites.

All PCTU SOPs with regard to data management will be adhered to by the study team. A data management plan will be written to cover all aspects of managing the data.

#### Confidentiality

Information related to participants will be managed in accordance with General Data Protection Regulation (GDPR), NHS Caldecott Principles, The Research Governance Framework for Health and Social Care, and the conditions of Research Ethics Committee Approval.

The participant information sheets will set out arrangements relating to confidentiality, security, storage of data, and accessibility of data only to the study team. All paper documentation containing identifiable participant data such as consent forms and CRFs will be kept in locked filing cabinets at the NHS sites or at QMUL offices. All participants will be assigned a unique SURECAN participant ID. The CRFs will be pseudo-anonymised with the participant ID. The study team will keep logs that will contain personal information collected on participants to facilitate the running of the trial. These logs will be kept on a secure, password-protected shared drive, only accessible by appropriate study team members with the password. At participating sites, identifiable information of participants will be kept on secure NHS trust computers only accessible by site staff.

Data collected using REDCap will be pseudonymised by using the unique study participant ID. REDCap data is stored securely on the secure virtualised environment at the Barts Cancer Centre (BCC). The BCC environment requires dual factor authentication to access the portal and the folders where the data are stored are only accessible to the appropriate members of the PCTU and the SURECAN study team.

The audio recorded intervention session data will be collected using an encrypted audio recording device. Once the data has been collected, it will be stored on an encrypted USB and deleted from the audio recording device. Sessions recorded using the online video calling platform are saved directly onto the encrypted USB. The encrypted USBs will be securely returned to the study team.

### Statistical methods

#### Statistical methods for primary and secondary outcomes

Prior to any analysis taking place, a statistical analysis plan will be developed and made publicly available, containing a more detailed and technical description of the analysis to be performed. To ensure transparency and reproducibility, its content will follow the guidelines proposed by Gamble et al. [47].

The analysis will be reported in line with the CONSORT guidelines and the extension for non-pharmacologic treatment interventions [48]. Baseline demographic and clinical outcomes will be summarised by treatment group. Normally distributed data will be summarised by mean (standard deviation); non-normally distributed data will be presented as median (interquartile range) and categorical variables presented as *n* (%).

The analysis will follow intention-to-treat principles, where participants with available data are included in the treatment group to which they were randomised. Hypothesis tests will be two-sided and estimated treatment effects will be accompanied by a 95% confidence interval. For all analyses, a significance level of 5% will be used.

The primary analysis will be a mixed effects linear regression of the total FACT-G score at 52 weeks with a random effect for therapist, fixed effects for baseline score, and randomisation stratification factors. Secondary outcomes will be modelled similarly.

To explore the treatment effects over time, the analysis will be repeated with multilevel mixed effects models with a nested structure to include an additional random effect for individual, a fixed effect for time, and an interaction between treatment and time. Safety data will be summarised by treatment group.

Predictors of costs and cost-effectiveness will also be identified, the latter being calculated as the monetary value of QALYs minus therapy costs. Generalised or standard linear models will be used as appropriate.

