##### Secondary outcomes

The secondary outcomes and mediator measures shown below (unless specified) will be reported at all timepoints: baseline, 7 weeks, 16 weeks, 52 weeks, and 2 years (where applicable). The method of aggregation will be mean scores for both arms. Further details will be presented in the forthcoming statistical analysis plan.The total score of the FACT-G at all other timepointsThe FACT-G sub-scale total scores (physical well-being [range 0–28], social/family well-being [range 0–28], emotional well-being [range 0–24] and functional well-being [range 0–28]. With higher scores indicating better QoLFear of cancer recurrence [29]. Four question self-report scaleThe Impact of Cancer scale (IOCv2): positive and negative impacts subscales [30]Anxiety and depression, measured using the Hospital Anxiety and Depression Scale (HADS) [31]The Chalder Fatigue Scale (CFQ) [32] which is composed of 11 items, each of which is answered using a 4-point Likert scale ranging from 0 (less than usual) to 3 (much more than usual). The maximum score is therefore 33, and a higher score is associated with a worse health stateMeasuring independent physical activity (frequency of occurrences, and duration in minutes) using an modified version of the Godin leisure score index questionnaire [33]The EuroQol (EQ-5D-5L) [34] will be used to measure health-related QoL and to derive quality-adjusted life years (QALYs). The EQ-5D-5L consists of five domains (mobility, usual activities, self-care, pain/discomfort, and anxiety/depression). Each domain is scored between 1 (no problems) and 5 (extreme problems)Health and social care utilisation and use of informal care measured using an adapted version of the Client Service Receipt Inventory [35]. This will cover the three months before randomisation and the periods up to 16-week and 52-week follow-up. The CSRI will be self-completed by participants. We will also collect employment statusEngagement and frequency of engagement in any new meaningful activities (e.g. new work, job, hobbies, or interests) at 16- and 52-week follow-up. This will be analysed as a categorical variable and therefore represented as a descriptive table, for each arm

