#### Health economics

For the economic evaluation, we will combine health and social care costs with the primary outcome measure and quality-adjusted life years (QALYs). Costs will be calculated for the intervention based on therapist time required, and other costs will be derived from the CSRI combined with recognised unit costs. For a societal perspective, informal care and lost employment costs will be valued using average wage rates. QALYs will be estimated using the EQ-5D-5L combined with UK tariffs and using area under the curve methods [35]. Cost differences will be compared between the groups across the whole follow-up period using a regression model with adjustment made for baseline costs. QALY differences will adjust for baseline EQ-5D-5L. Cost-effectiveness will be assessed from a health and social care perspective. If the intervention results in higher costs and better outcomes, then we will divide incremental costs (intervention minus usual care) by incremental QALY to generate an incremental cost-effectiveness ratio. Uncertainty around the cost-effectiveness results will be explored using cost-effectiveness planes and acceptability curves from 1000 cost-outcome combinations from bootstrapped regression models. The cost per unit improvement on the FACT-G will also be calculated. To assess the long-term cost-effectiveness of ACT+, we will develop a decision model using Markov processes. This will entail defining health states over time to which costs and QALYs will be attached. The structure of the model will be developed within the early stages of the programme and will consist of states defined both by clinical severity and quality of life. Costs and probabilities for the model will be derived from published literature, the trial, and expert opinion. The model will be subjected to extensive deterministic and probabilistic sensitivity analyses.

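### The outcome for the predictors-of-cost-effectiveness analysis subtracts therapy costs alone, which does not match the health and social care perspective set for the economic evaluation

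*Protocol article*

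**What the plan says.** The definition is in the protocol article, *Statistical methods for primary and secondary outcomes*. The plan is to look for predictors of cost and of cost-effectiveness, "the latter being calculated as the monetary value of QALYs minus therapy costs". The models are to be linear, in standard or generalised form.

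The *Health economics* section describes the economic evaluation itself:

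- Perspective: "Cost-effectiveness will be assessed from a health and social care perspective".
- Components: "Costs will be calculated for the intervention based on therapist time required, and other costs will be derived from the CSRI".
- Main comparison: if ACT+ costs more and does better, "we will divide incremental costs (intervention minus usual care) by incremental QALY to generate an incremental cost-effectiveness ratio".

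Under *Secondary outcomes*, the instrument that supplies the non-intervention costs is listed: "Health and social care utilisation and use of informal care measured using an adapted version of the Client Service Receipt Inventory". It covers the three months before randomisation and the periods up to the 16-week and 52-week follow-ups.

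**The concern.** QALYs valued in money less a cost is a net-benefit measure, although the article does not use that term. Net benefit is coherent only if the cost subtracted is the full cost under the chosen perspective. Here the article attaches two different cost definitions to the word cost-effectiveness. The evaluation counts intervention and other health and social care costs; the predictor analysis, on its plain wording, counts the first component alone.

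This is a stated definition and not a detail left to a later plan. An analyst who follows it literally will compute an outcome that does not correspond to cost-effectiveness as described under *Health economics*. A patient characteristic that goes with heavy use of NHS or social care would leave no trace in that outcome, except through any link with QALYs or with therapy received. The trial could then report predictors of cost-effectiveness that do not predict it under its own perspective.

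**Working it through.** The article states no figure for this quantity, so there is nothing to reproduce. The check is algebraic, with an illustration on assumed values.

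**Notation.** For participant *i*: Q = QALYs, T = therapy (intervention) cost, O = other health and social care cost from the CSRI, λ = money value of one QALY.

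**Two definitions**

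- *Statistical methods*, as written: NB = λQ − T.
- *Health economics* perspective: NB = λQ − (T + O).
- Difference for each participant: O.

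The two agree for every participant only if O is zero for all. They give the same predictor coefficients only if O is unrelated to the predictors. The article assumes neither.

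**Effect on a predictor.** In a standard linear model, coefficients are additive in the outcome. Let a characteristic have coefficients b_Q on QALYs, b_T on therapy cost and b_O on other costs.

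- As written: λb_Q − b_T.
- Full cost: λb_Q − b_T − b_O.

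The written outcome drops b_O entirely.

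**Usual-care arm.** If therapy means ACT+, then T = 0 for participants on usual aftercare alone and the outcome reduces to λQ. In that arm, predicting cost-effectiveness is the same as predicting QALYs.

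**Size in QALY terms (assumed values).** Take two participants with the same QALYs and therapy cost who differ in O.

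| Difference in O | λ = £20,000 | λ = £30,000 |
|---|---|---|
| £500 | 500/20,000 = 0.025 QALY | 500/30,000 = 0.017 QALY |
| £1,000 | 1,000/20,000 = 0.050 QALY | 1,000/30,000 = 0.033 QALY |

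The outcome as written scores the two participants identically in every cell.

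**Can a sign change? (assumed values).** Take b_Q = 0.02 and b_T = £800.

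- λ = £20,000, as written: 20,000 × 0.02 − 800 = −£400, whatever b_O is. Full cost: +£100, −£400 or −£900 for b_O = −£500, £0 or +£500.
- λ = £30,000, as written: 30,000 × 0.02 − 800 = −£200. Full cost: +£300, −£200 or −£700 for the same values of b_O.

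So the direction of an apparent predictor can reverse. These inputs are illustrative and are not estimates for this trial.

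**The case against.** **The main economic evaluation is sound.** A reader might infer that the trial's cost-effectiveness result leaves out service costs. The article does not support that. The defective sentence introduces a search for predictors and governs nothing else. The ratio, the bootstrapped planes and the acceptability curves are set out under *Health economics*, where "we will combine health and social care costs with the primary outcome measure and quality-adjusted life years (QALYs"). No between-arm net benefit is planned from the defective formula. This objection stands and limits the point to one supplementary analysis.

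**Service use stays visible elsewhere.** The same sentence also plans predictors of costs, without restricting them to therapy, and costs are compared between arms. This too stands. It does not repair the cost-effectiveness outcome, which would still be mislabelled.

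**The wording may be loose drafting for total costs.** That is possible. But *Health economics* separates intervention cost from other costs, so therapy costs most naturally means the first. If total costs were intended, the correction costs nothing.

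**Controls may have therapy costs.** The protocol's survey of usual aftercare found counselling (61%) and CBT (16%) among the interventions offered, and the eligibility criteria exclude another psychological intervention only if it is current at entry. Zero cost for every control therefore holds only if therapy means ACT+ alone, which the article does not say. This is a fair qualification. Under the wider meaning, the remaining health and social care costs are still left out.

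**Training, supervision and the handbook.** A reader might also infer from the therapist-time sentence that these are wrongly omitted from the intervention cost. The article does not say that therapist time is the sole element, supervision could fall within it, and itemised costing is commonly left to a fuller plan. Whether to count one-off training is a debatable costing choice. No error is shown there.

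**Conclusion.** The inconsistency is real and should be fixed. The person-level outcome for the predictor analysis, as worded, leaves out the CSRI-derived health and social care costs that the article's own perspective requires. The error for each participant equals that participant's other health and social care cost. For a predictor in a standard linear model, it equals the predictor's association with those costs.

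The conclusion rests on reading therapy costs as narrower than total health and social care costs, which is the natural reading given how the components are separated. How far the set of identified predictors would change cannot be judged from the article, because it gives no cost data or QALY threshold; the pound and QALY figures above are assumed. The primary outcome, the sample size, the clinical analysis and the main cost-effectiveness results are untouched, so this falls short of a must-fix.

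**What to change.** In *Statistical methods for primary and secondary outcomes*, replace therapy costs with *total health and social care costs (intervention plus CSRI-derived costs)*, so that net benefit = QALYs × stated threshold(s) − total health and social care costs. Two details keep this aligned with *Health economics*:

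- Use follow-up costs over the same period as the QALYs. The three months before randomisation belong in the model as baseline adjustment, as already planned for the cost comparison.
- Leave informal care and lost employment out of this version, since the article places them under a societal perspective.

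The threshold value or range can be given in the analysis plan.

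The change is to wording and needs no new data. The outcome will require CSRI as well as EQ-5D-5L responses, but the shortened questionnaire offered to reluctant participants already includes both. Adding service costs may make the outcome more variable and the predictor estimates less precise, which is the price of analysing the quantity that the label claims.

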#### Interim analyses

No formal interim analyses comparing outcome data between the two groups is planned.

#### Methods for additional analyses (e.g. subgroup analyses)

The primary analysis will be repeated to include an interaction term for the treatment effect and potential moderators (subgroups/moderators). Subgroups will include factors such as age, gender, type of cancer, severity of depression, and the effects loneliness and worry in relation to COVID-19 at baseline. Full details of additional analyses will be included in an analysis plan.

#### Methods in analysis to handle protocol non-adherence and any statistical methods to handle missing data

Sensitivity analyses of the primary analysis will be conducted (i) on the subsample who adhere to the protocol (ii) to explore the dose-response relationship between intervention attendance and outcome and (iii) to assess the robustness of the primary conclusions to the missing data assumptions. Multiple imputation will be undertaken, provided we have strong predictors of missingness and an appropriate imputation model. Diagnostic checks will be performed to assess this.

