#### Intervention

ACT is an intervention that aims to increase psychological flexibility. Psychological flexibility refers to an individual’s ability to adapt to demands, shift perspectives, and balance competing desires and needs [16, 23–25]. This means that ACT could help a patient to accept what cannot be changed (e.g. that the cancer might recur), while committing themselves to the things they can change (i.e. meeting their goals in life, irrespective of having had cancer).

We developed the intervention to be integrated with options for work/vocational activity support and exercise in ways that are tailored to each participant’s personal values and goals, and therefore called this ‘ACT Plus (+)’. We also developed a participant handbook and manuals for therapists. The process of developing and refining the ACT+ intervention will be reported separately elsewhere (in preparation).

The intervention is delivered by therapists who had undergone specifically designed training in ACT+ led by the senior study therapist (co-chief investigator TC). Full details of the SURECAN ACT+ training and its evaluation have been published [26]. The core professions of the therapists include clinical psychologists, high intensity therapists (from NHS Talking Therapies), cognitive behaviour therapists trained in ACT, and trained counsellors. Treatment integrity will be assessed at the end of the trial guided by Perepletchikova et al.’s treatment integrity procedures checklist [27].

The sessions can be delivered face-to-face (at the therapist’s main practice), by phone or via online video calls, according to participant preference. The intervention involves up to eight sessions delivered at weekly or fortnightly intervals. Sessions last around 1 h and include homework to be completed prior to the next session. All sessions should take place within a range of 14–20 weeks from a participant being allocated to the intervention arm at randomisation (depending on the frequency of sessions, i.e. weekly or fortnightly, and allowing occasions for missed/rescheduled sessions). Participants are also provided with the ACT+ participant handbook. Eligible participants randomised to the intervention arm will receive the ACT+ intervention in addition to usual aftercare.

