#### Criteria for discontinuing or modifying allocated interventions

Intervention arm participants may discontinue receiving the intervention at any point they request.

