#### Adverse events

All adverse events (AE) and severe adverse events (SAE) as defined (see the ‘Adverse event reporting and harm’ section) will be reported in the trial analysis by arm. In addition, we will report the proportion of patients who deteriorate on the FACT-G and HADS at 52 weeks from baseline, where at least four ACT+ sessions (50%) were delivered (Figs. 2 and 3) [46].

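### If adherence means attending ACT+ sessions, the planned rerun on adherers is not a randomised comparison and says little about the robustness of the intention-to-treat result

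*Protocol article*

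**What the plan says.** The section of the protocol article on protocol non-adherence and missing data opens with "Sensitivity analyses of the primary analysis will be conducted" and lists three items. The first two are "i) on the subsample who adhere to the protocol (ii) to explore the dose-response relationship between intervention attendance and outcome". The third concerns the missing-data assumptions. No complier-effect or instrumental-variable estimate is named there.

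The statistical methods section sets the main principle: "The analysis will follow intention-to-treat principles, where participants with available data are included in the treatment group to which they were randomised". The model is given as "The primary analysis will be a mixed effects linear regression of the total FACT-G score at 52 weeks with a random effect for therapist", with baseline score and stratification factors as fixed effects. A separate statistical analysis plan is promised, "containing a more detailed and technical description of the analysis to be performed".

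Two other sections show how adherence arises. Under Intervention: "The intervention involves up to eight sessions delivered at weekly or fortnightly intervals". Under the criteria for discontinuing: "Intervention arm participants may discontinue receiving the intervention at any point they request". The only attendance threshold in the article is under Adverse events, where deterioration is to be reported "where at least four ACT+ sessions (50%) were delivered". It is not offered there as a definition of adherence.

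**The concern.** Sessions are offered in one arm only, and a participant can stop on request. An attendance-based adherer is therefore someone selected by events and choices after randomisation. The usual-care participants who would have attended cannot be identified, so there is no like-for-like control group for the selected ACT+ participants.

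Whatever drives attendance, such as motivation, general health or recurrence, may also drive FACT-G at 52 weeks. Adjusting for baseline FACT-G and stratification factors cannot remove differences that arise after baseline. The adverse events section says that hospitalisation for recurrence will not be collected as an adverse event, and self-reported service use would capture it only in part.

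The label matters too. A sensitivity analysis asks the same question under different assumptions, as the missing-data item does. The adherer rerun asks a different question. What is at stake is interpretation: a small or null intention-to-treat effect could appear beside a larger adherer effect that reflects selection, and be read as evidence that enough sessions work.

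**Working it through.** **The plan's own figures.** The point disputes no stated number, but the check borrows the planning values.
- Effect size 0.4, two-sided 5%, 90% power: the t-based calculation gives 132.3, so 133 per arm and 266 in total, as stated.
- Design effect: 1 + (10 − 1) × 0.01 = 1.09. Then 266 × 1.09 / 0.85 = 341.1 (342 with rounding per arm), within 1% of the stated 344.
- Implied SD: 6 / 0.4 = 15 points.
- Expected with 52-week data: 344 × 0.85 = 292.4, or about 146 per arm.

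**Bias with no true effect.** Let p be the proportion who would adhere if offered ACT+, with untreated 52-week means μ_a for them and μ_n for the rest. Randomisation puts the same mix in both arms.
- Control mean = p·μ_a + (1 − p)·μ_n.
- ACT+ adherer mean = μ_a.
- Difference = (1 − p)(μ_a − μ_n).

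The article gives neither p nor the gap. Both are assumptions here: p from 60% to 90%, and a correlation r from 0 to 0.3 between propensity to attend and untreated FACT-G. Simulated bias in points (SD 15, one million per arm, no baseline adjustment):

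| Adherence | r = 0 | r = 0.1 | r = 0.2 | r = 0.3 |
|---|---|---|---|---|
| 60% | 0.0 | 0.99 | 1.94 | 2.87 |
| 70% | 0.0 | 0.77 | 1.50 | 2.24 |
| 80% | 0.0 | 0.49 | 1.06 | 1.59 |
| 90% | 0.0 | 0.28 | 0.59 | 0.86 |

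The formula agrees. At 60% and r = 0.3 the simulated gap is 7.29, and 0.4 × 7.29 = 2.92 against 2.87. At 90% and r = 0.1 the gap is 2.97, and 0.1 × 2.97 = 0.30 against 0.28.

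**Error rate.** With 146 per arm and no true effect, the nominal 5% test of adherers against all controls rejects in about 9–17% of trials at r = 0.2 and 13–30% at r = 0.3, for adherence of 60–80%. Intention to treat stays near 5%.

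**A crude attendance contrast.** If the dose-response analysis compared adherers with non-adherers inside the ACT+ arm, the bias would be the whole gap: about 2.5–3.0, 4.8–5.9 and 7.3–8.8 points at r = 0.1, 0.2 and 0.3. The article does not say that it will be done this way.

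**The randomisation-based estimate.** Complier effect = intention-to-treat difference / p.
- With no true effect it stays at 0 in every cell.
- With a true 6-point effect in adherers only, it returns about 6.0. Adherers against all controls gives 6.3 to 8.9 for r = 0.1–0.3.

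**Its precision.** SE of the intention-to-treat difference = 15 × √(2/146.2) = 1.75. Applying the design effect to both arms, which is conservative, gives 1.75 × √1.09 = 1.83. Dividing by p gives 3.05, 2.62, 2.29 and 2.04 at 60, 70, 80 and 90%. Estimate and SE are both divided by p, so to this approximation the test of no effect is the same as for intention to treat.

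**Its weak point.** If allocation also helps those below the receipt threshold by b points, the intention-to-treat difference gains (1 − p)·b and the complier estimate is too large by b(1 − p)/p.

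**The case against.** The strongest reply is that much is left to the analysis plan, which is not shown. Four parts of it stand.

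- A reader might infer that both adherence analyses are confounded. The article does not support that for the dose-response item. It names no estimator, and sessions instrumented by arm would be a dose-response analysis that fits its wording.
- Adherence to the protocol is not defined. It could cover deviations in either arm, such as eligibility errors, and the comparison of adherers with all controls is itself an assumption. The point applies where adherence means attendance.
- A reader might attach one figure to the bias, such as a fixed share of the 6-point target. The article gives no adherence rate and no prognostic gap. Baseline adjustment would be expected to shrink the bias. The direction is not certain either: people who improve early may stop, which could lower the correlation or reverse its sign.
- The complier estimate has assumptions of its own. People who attend a few sessions, or hold only the participant handbook, may benefit.

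What does not stand is that the analysis plan could rescue the adherer rerun. The article fixes that analysis, and no attendance-based definition of adherence makes the selected subsample a randomised comparison.

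**Conclusion.** The point holds for the adherer rerun, on the condition that adherence means ACT+ attendance. It holds for the dose-response analysis only if outcome is simply related to attendance.

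The illustrative bias is 0 if attendance is unrelated to prognosis, and about 0.3 to 2.9 FACT-G points under the assumed ranges (60–90% adherence, r = 0.1–0.3, SD 15, no baseline adjustment). These are not estimates for this trial.

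A reader might infer that the trial's main conclusion is at risk. It is not: the primary analysis is by intention to treat, and its estimate and error rate are untouched. A reader might also take the four-session mark as the plan's adherence definition, but it is used only for the deterioration report. This is an inexpensive improvement to the supporting analyses, not a flaw in the primary one.

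**What to change.** - Make a complier average causal effect the main non-adherence analysis, for example by two-stage least squares, with randomised arm as instrument, the primary-model covariates and allowance for therapist clustering.
- Drop the rerun on adherers, or keep it labelled as descriptive.
- Estimate the dose-response relationship with number of sessions instrumented by arm.
- Call these supplementary estimands, and keep the term sensitivity analysis for work that targets the primary estimand, such as the missing-data item.
- Define receipt of the intervention for this analysis and justify the threshold. The four-session mark should not be carried over without a reason.
- State the assumptions: no effect of allocation below the threshold, whether from fewer sessions or the handbook, and a linear effect per session in the dose version.

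The cost is some programming and a wider interval: an SE of about 2.0 to 3.1 points against 1.8 for intention to treat, at 60–90% adherence with SD 15. The result also relies on the exclusion restriction. No new data and no change in sample size are needed.
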